## **Introduction**

Low back pain (LBP) is a significant issue with considerable impact on people’s lives and economies. From 1990 to 2019, the global incidence of LBP increased by 50% ^[1]^, and is now the leading cause of disability worldwide. It has remained top-ten-ranking causes of disability adjusted life years (DALY) ^[2]^. In 2019, it was estimated 223.5 million people have LBP and 63.7 million LBP-related DALYs worldwide.^[1,2]^ South Asia is also home to the highest number of people with LBP (96.3 million) among all regions of the world ^[3]^ and India being the largest country in South Asia accounts nearly about 8% people yearly lived with disability (YLD) due to LBP.^[4]^ LBP is the leading health condition contributing to the need for rehabilitation services ^[5]^ and it is estimated that the number of people with low back pain will increase in the future, and even more rapidly in low-income and middle-income countries.^[6]^

The underlying mechanisms of symptom onset and progression are highly variable, complicated and heterogeneous in low back pain, thus treatment approaches to lessen LBP have proven to be extremely difficult.^[7,8]^ .Various methods (or approaches) have been proposed and tried to optimize clinical decision making in LBP, such as the use of classification systems or CPRs with varying degrees of success^[7,9-17]^. Despite this, there is a global evidence-to-practice gap for treating LBP, and these treatment guidelines are not being adopted as recommended. ^[6,18-23]^

Consistent recommendations from international guidelines have been made in recent years, indicating conservative physiotherapy intervention is useful in treating LBP. Individuals with acute LBP should get conservative treatments including encouragement to stay active, education about the benign nature of LBP, and assurances regarding the absence of significant pathology.^[10,24-35]^ However, treatment based on the biopsychosocial model of care should be given to people who are at risk of acquiring chronic pain and impairment. ^[7,8,10,22-29]^ and also patients with CLBP.^[36]^ Also, in CLBP its is more flexible, multidimensional, clinically-reasoned approach to profile patient complexity may be required to inform individualised, patient-centred care.^[37]^ which can lead to healthcare cost savings and better return to work and by implication a better economical outcome for the patient^.[38]^

Although, various randomized controlled trials (RCT) are have been conducted on variety of classification and stratification system on LBP like Start back approach, Treatment-Based Classification (TBC) , Mechanical Diagnosis and Therapy (MDT), the Cognitive Functional Therapy (CFT), Movement System Impairment (MSI) or, Pathoanatomical-Based Classification (PBC),^[12,39-43]^ , there is currently insufficient evidence supporting the use of any classification systems for managing LBP in clinical practice.^[10, 44]^ The randomized controlled trials (RCTs) upon which guideline recommendations are based typically show small effect sizes of questionable clinical importance ^[18,32,44,45].^ A potential reason for the limited effects demonstrated in RCTs is at misunderstandings that NSLBP is a homogeneous group. ^[46,47]^

While the STarT back approach and Cognitive Functional Therapy (CFT) integrate risk stratification as a viable strategy to screen for the risk of patients experiencing poor outcomes in terms of pain and disability based on psychosocial variables, the Mechanical Diagnosis and Therapy (MDT), Pathoanatomical-Based Classification (PBC), and Movement System Impairment (MSI) approaches primarily treat mechanical dysfunction regardless of psychosocial presentation. Recent guidelines, however, encouraged, to incorporate the treatment- and mechanism-based categorization systems as well as psychological component throughout the patient's examination. ^[10,48]^ Thus, most the treatment strategies fail to consider the multidimensional nature of LBP^[7,8,10,22-29,36-39]^ and patho-anatomical factors despite emerging evidence, that they may be important in clinical decision-making.^[49-53]^

Therefore, recent guidelines have highlighted drawbacks that necessitate the consideration of a classification system that combines the biomechanical and psychological aspects of LBP in a more comprehensive way. The value of individualized or personalized interventions includes education, counselling, exercise, mobility training, and manual therapy, depending on the patient's clinical features and examination ^[10,48,54]^ and recommend decision making to have interim evaluations that should be scheduled to track patient progress and advise the revision of the intervention strategies and tactics accordingly. ^[10]^ Explicit information regarding the dosage, duration, and other aspects of how the indicated treatments should be administered should also be provided. ^[55]^

The Specific Treatment Of Problems of the Spine (STOPS) is a classification system of LBP that is based on the biopsychosocial model of care.^[56]^ The basic premise of the STOPS approach is that LBP is multifactorial, and factors other than the pathoanatomical source of pain (e.g., nociceptive source of symptoms) need to be considered in a robust classification system including neurophysiological (e.g., central sensitization) and psychosocial components (e.g., fear-avoidance) of the pain.^[56]^ Based on this philosophy, the STOPS approach was developed where patients are sub-grouped and treatment strategies are individualised to the participant’s presentation ^[56-60]^ and series of studies has been investigated in Australia and has been proven to be effective in a subgroup of individuals with LBP in that country. ^[14,61-65]^

**Need for the study:**

The STOPS approach is yet to be investigated in a different country and setting than where it was initially developed. Research has showed evidence-to-practice gap for treating LBP, and these treatment guidelines are not being adopted as recommended in India. ^[18,20]^ Despite the high incidence of LBP, where caste, economic status, religion, and even geographic location (rural or urban) are recognized socio-cultural barriers to healthcare seeking, India lacks effective and targeted treatment methods based on the biopsychosocial model of care, which exacerbates disability and widens the gap between India and affluent countries in terms of LBP care.^[4,5,6,18]^  These findings indicate that the quality of physiotherapy care for LBP in India needs to be optimized.

## LITERATURE REVIEW

| Sl. No | 1 |
| --- | --- |
| Author | Muhammed Rashid, T. Muhammad, Shobhit Srivastava |
| Tittle | Back pain and treatment seeking among community-dwelling older adults: Findings from a population-based survey. |
| Objective | To explore the prevalence and factors associated with back pain and types of treatment seeking of older people with back pain. |
| Study | Cross-sectional design has been conducted using a population-based survey of the Longitudinal Ageing Study in India |
| Sample size | 31,464 older adults |
| Outcome measure | Questionnaire used to assess back pain and treatment seeking |
| Results and  Conclusion | Out of the participants experiencing back pain, approximately 34% sought relief. Among them, the majority, accounting for 46.2%, opted for external applications, followed by 40.8% who turned to analgesics, and only 6.6% who pursued therapy. Notably, older adults with a higher level of education were more likely to choose therapy compared to those with little or no education. Furthermore, participants from the wealthiest quintile demonstrated a greater inclination towards therapy compared to those from the lowest quintile. Despite being globally recommended as the primary approach to managing back pain, therapy was the least utilized method and should be actively promoted. |

| Sl. No | 2 |
| --- | --- |
| Author | Supreet Bindra, Sinha A.G.K, and Benjamin A.I |
| Tittle | Epidemiology of Low Back Pain in Indian Population: A Review |
| Objective | Describing the epidemiology of LBP in terms of prevalence, demographic features, risk factors, impact and health care service utilization for LBP in Indian context |
| Study | Review |
| Search engine | Databases such as Pub med, Research gate and Google scholar |
| Conclusion | When it comes to seeking healthcare services for lower back pain (LBP), a significant number of individuals chose not to consult any professional. The next commonly adopted approach was self-medication with over-the-counter drugs, while a majority of people preferred traditional treatments over the allopathic system of medicine. Factors such as low socioeconomic status, limited education, past history of LBP, physical aspects like lifting heavy objects, engaging in repetitive or static postures, and psychosocial factors such as anxiety, depression, job dissatisfaction, lack of control over work, mental stress, long working hours, and obesity were found to be associated with LBP. However, it should be noted that the existing literature on LBP in the Indian population lacks conclusive evidence due to various reasons. These include small sample sizes in studies, lack of consistency in defining LBP, diversity among the populations under study, insufficient epidemiological research in the general population, and inadequate analysis of risk factors, which restricts the generalizability of the findings. |

| Sl. No | 3 |
| --- | --- |
| Author | Joshua Zadro, Mary O’Keeffe, Christopher Maher |
| Tittle | Do physical therapists follow evidence-based guidelines when managing musculoskeletal conditions? Systematic review |
| Objective | To determine what percentage of physical therapy treatment choices for musculoskeletal conditions agree with management recommendations in evidence-based guidelines and systematic reviews. |
| Study | Systematic review. |
| Sample size | Performed searches in Medline, Embase, Cumulative Index to Nursing and Allied Health Literature, Cochrane Central Register of Controlled Trials, Allied and Complementary Medicine, Scopus and Web of Science combining terms synonymous with ‘practice patterns’ and ‘physical therapy’ from the earliest record to April 2018. Studies that quantified physical therapy treatment choices for musculoskeletal conditions through surveys of physical therapists, audits of clinical notes and other methods. Included 94 studies |
| Outcome measure | Using medians and IQRs, they summarised the percentage of physical therapists who chose treatments that were recommended, not recommended and had no recommendation, and summarised the percentage of physical therapy treatments provided for various musculoskeletal conditions within the categories of recommended, not recommended and no recommendation. Results were stratified by condition and how treatment choices were assessed (surveys of physical therapists vs audits of clinical notes). |
| Results and  Conclusion | Many physical therapists seem not to follow evidence-based guidelines when managing musculoskeletal conditions. There is considerable scope to increase use of recommended treatments and reduce use of treatments that are not recommended. |

| Sl. No | 4 |
| --- | --- |
| Author | Nadia Corp, Gemma Mansell, Siobhán Stynes, Gwenllian Wynne-Jones, Lars Morsø, Jonathan C. Hill, Danielle A. van der Windt |
| Tittle | Evidence-based treatment recommendations for neck and low back pain across Europe: A systematic review of guidelines |
| Objective | To synthesized evidence from European neck and low back pain (NLBP) clinical practice guidelines (CPGs) to identify recommended treatment options for use across Europe |
| Study | Systematic review |
| Sample size | Comprehensive searches of thirteen databases were conducted, from 1st January 2013 to 4th May 2020 to identify up-to-date evidence-based European CPGs for primary care management of NLBP, issued by professional bodies/organizations |
| Outcome measure | The AGREE II checklist was used to critically appraise guidelines. |
| Results and  Conclusion | Low back pain the guidelines recommended entirely non-pharmacological treatments, additionally including work-based interventions, advice/programmes to return to work for specific subgroups |

| Sl. No | 5 |
| --- | --- |
| Author | Nafisa Fidvi & Stephen May2 |
| Tittle | Physiotherapy Management of Low Back Pain in India- A Survey of Self-reported Practice |
| Objective | To explore the self-reported management strategies employed by physiotherapists in India as it is unknown if these are in line with contemporary guidelines. |
| Study | Cross-sectional survey study |
| Sample size | 350 physiotherapists |
| Outcome measure | self-completed questionnaire |
| Results | All therapists reported that they gave some kind of advice to patients, used exercises and electrotherapy, and in addition about half used manual therapy. The majority of therapists used 8–12 sessions of treatment. |
| Conclusion and limitations | Indian physiotherapy management of low back pain has shown several areas of ‘good practice’ in line with contemporary guidelines. It also highlighted potential areas of concern regarding evidence-based practice; namely, very common use of passive electrotherapy modalities and potential excessive treatment. This report has implications for physiotherapy practice and education in India.  limitation of this study is that it does not characterize between cases of  Acute and chronic LBP according to guideline recommendation. These findings were from one of state i.e. Maharashtra. |

| Sl. No | 6 |
| --- | --- |
| Author | Jon J Ford, Andrew J Hahne, Luke D Surkitt, Alexander Y P Chan, Matthew C Richards, Sarah L Slater, Rana S Hinman, Tania Pizzari, Megan Davidson, Nicholas F Taylor |
| Tittle | Individualised physiotherapy as an adjunct to guideline-based advice for low back disorders in primary care: a randomised controlled trial |
| Objective | This study investigates whether individualised physiotherapy plus guideline-based advice results in superior outcomes to advice alone in participants with low-back disorders. |
| Intervention | prospective parallel group multicentre randomised controlled trial was set in 16 primary care physiotherapy practices in Melbourne, Australia. Random assignment resulted in 156 participants receiving 10 sessions of physiotherapy that was individualised based on pathoanatomical, psychosocial and neurophysiological barriers to recovery combined with guideline-based advice, and 144 participants receiving 2 sessions of physiotherapist-delivered advice alone. |
| Sample size | Sample size 300 |
| Outcome measure | Primary outcomes were activity limitation (Oswestry Disability Index) and numerical rating scales for back and leg pain at 5, 10, 26 and 52 weeks postbaseline. Analyses were by intention-to-treat using linear mixed models. |

## Methods

## 2.1 Study design

This study is blinded, two armed parallel Randomized Controlled Trial (RCT), will examine the effectiveness of Specific Treatments for the Problems of Spine (STOPS) Physiotherapy care for the management of Low Back Pain (LBP) in comparison with standard physiotherapy (usual care).An overview of process of study is presented in Figure 1.

Assessed for eligibility

(n = …)

# Enrollment

Excluded (n = …) Not meeting inclusion criteria

(n = …)

Refused to participate (n = …)

Other reasons (n = …)

Randomized (n = 150)

Allocated to Usual care intervention

(n = 75)

Received allocated intervention (n = …)

Did not receive allocated intervention (n = …)

(give reasons)

Allocated to Individualised intervention

(n = 75)Received allocated intervention (n = …)

Did not receive allocated intervention (n = …)

(give reasons)

**Allocation**

**Follow up**

Lost to follow up

(n = …) (give reasons)Discontinued intervention (n = …) (give reasons)

Lost to follow up

(n = …) (give reasons)Discontinued intervention (n = …) (give reasons)

# Analysis

Analyzed (n = …)

Excluded from analysis

(n = …) (give reasons)

Analyzed (n = …)

Excluded from analysis

(n = …) (give reasons)

FIGURE 1: Consort flow Chart

## 2.2 Registration and ethics

This study will be registered in Clinical Trials Registry- India (CTRI). The study protocol will be reviewed and approved by the institutional ethical committee of JSS Academy of Higher Education and Research, Mysuru, India. The Consolidated Standards of Reporting Trials (CONSORT) guidelines will be followed to report the study. Consent of the participant will be obtained before the commencement of the study.

## 2.3 Setting

The study will be conducted at Physiotherapy Outpatient Department (OPD) of JSS Hospital, Mysuru, India and the associated community centers affiliated to JSS Hospital.

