## 2.4 Recruitment strategy

Patients with LBP visiting Physiotherapy OPD of JSS Hospital, Mysuru, India and patients who are part of the community outreach programs of JSS College of Physiotherapy in Mysuru, will be invited to participate in this study. The convenience sampling will be followed for the recruitment. Individuals who express interest in the study will be given detailed information regarding their involvement and the specifics of the study.

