## 2.5 Sample size estimation

Sample size was calculated using G power using input parameters such as an effect size of 0.5, and power of 0.95. A sample size of 154 was received as an output from G power, allowing for loss to followup.

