**Table 2: Patient outcome measures**

## 2.9 Randomization and allocation concealment

Eligible participants will be randomized in to STOPS group or standard physiotherapy group using web based open source randomization software, by a researcher who is not involved in any other phase of the study (participant screening or enrolment).

To ensure an equal number of participants in both groups and reduce allocation bias, the allocation will be concealed through block randomization. The administrator will create sealed envelopes with allocation information, which will be given to participants by the assessor after the baseline assessment is completed. Both patients and outcome evaluators will be blinded to group allocation.

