***Analysis of patients’ clinical outcomes***

A descriptive summary of the characteristics of the patients will be provided at baseline. Continuous outcomes for patients will be analysed using linear mixed models (group × time interaction, with time modelled as a repeated measure) adjusting for baseline score. Ordinal outcomes will be analysed using the Mann-Whitney U test, while the risk ratio and number needed to treat will be evaluated using χ2 analyses. Analyses will focus on detecting between-group effects (with 95% CIs) at each time point (5, 10, and 26 weeks), and participants will be dichotomized according to whether they achieve the minimal clinically important difference (MCID) on outcome measures or not. The MCID for participants will be defined as 10/100 points for the Oswestry, 2/10 for the BPI pain scales, at least ‘much improved’ on the global rating of change scale, and ‘very satisfied’ on the treatment satisfaction scales. Given that these values may be too low in some contexts, the analyses will be repeated using a threshold of 50% reduction in Oswestry and NRS pain scores [14,56]. All data will be analysed according to intention-to-treat analysis (ITT), with missing data handled via maximum likelihood estimation ^[114]^.

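### Patients are recruited and treated at a hospital OPD and at community centres, but the allocation is not said to be stratified by setting and the model has no setting term: a cheap, minor improvement

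*Protocol*

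**What the plan says.** Section 2.3 gives the setting as the "Physiotherapy Outpatient Department (OPD) of JSS Hospital, Mysuru, India and the associated community centers affiliated to JSS Hospital". Section 2.4 has two recruitment streams: patients attending the OPD, and "patients who are part of the community outreach programs of JSS College of Physiotherapy in Mysuru". It adds that "The convenience sampling will be followed for the recruitment", so no quota controls the mix. Table 3 (section 2.10.2) lists both kinds of location for both arms.

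Section 2.9 allocates patients "using web based open source randomization software, by a researcher who is not involved in any other phase of the study". On the method it says: "To ensure an equal number of participants in both groups and reduce allocation bias, the allocation will be concealed through block randomization". Its stated aims are equal numbers per arm and less allocation bias; balance by setting is not among them. The section gives no stratification factor, block size or number of lists.

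Under Analysis of patients' clinical outcomes, continuous outcomes are analysed by "linear mixed models (group × time interaction, with time modelled as a repeated measure) adjusting for baseline score". No term for setting is named.

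**The concern.** Blocks drawn across a mixed stream of patients balance the arm totals. They do not balance the arms within the OPD or within the community centres. One arm can therefore hold more community patients by chance, and the model as described would not adjust for it.

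This matters only if setting is related to outcome. The protocol gives some reason to think it might be. Need for the study lists economic status and rural or urban location among barriers to seeking care. The first entry in the Literature review reports that older adults with more education and wealth were more likely to choose therapy. Usual care, left to the treating physiotherapist's discretion in Table 3, could also vary by location. If setting is prognostic, leaving it out of both the allocation and the model adds avoidable noise to the Oswestry comparison.

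**Working it through.** The protocol gives no figure on this point to reproduce. It states neither the split between sources nor any outcome difference between them, so both are assumptions here.

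**Inputs**
- 150 patients, 75 per arm (Figure 1). Section 2.5 says 154, which barely changes the results below.
- Community share p: assumed 10% to 50%.
- Block size: assumed 4 in the simulation.
- Setting effect left after baseline adjustment: assumed 5 Oswestry points, or 0.2 to 0.5 SD.
- Yardsticks: the planned effect size of 0.5 (section 2.5), and the Oswestry effects of the earlier STOPS trial (Literature review, entry 6), which were 4.7 points (95% CI 2.0 to 7.5) at 10 weeks, 5.4 at 26 weeks and 4.3 at 52 weeks.

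**Step 1: chance imbalance without stratification.** For an equal split of 150 patients, the SD of the between-arm difference in community share is 2 × √(p(1 − p)/149). At p = 0.3 this is 2 × √(0.21/149) = 0.075. The exact columns use the hypergeometric distribution. The simulated columns use blocks of 4 on one list, with each patient's source drawn at random.

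| Community share | SD, formula (points) | SD, simulated | 10 points or more, simulated | 10 points or more, exact | 15 points or more, exact |
|---|---|---|---|---|---|
| 10% | 4.9 | – | – | 3% | 0.1% |
| 20% | 6.6 | 6.5 | 12% | 15% | 2.4% |
| 30% | 7.5 | 7.4 | 18% | 15% | 3.2% |
| 40% | 8.0 | 8.0 | 21% | – | – |
| 50% | 8.2 | – | – | 19% | 5.0% |

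The two methods agree on the SD. Their tail figures differ by a few points because patients come in whole numbers: in the exact calculation, 10 points of 75 is 7.5 patients, which means a difference of at least 8 when there are 30 community patients and at least 9 when there are 45. Simulation puts 15 points or more at about 2% to 6% of trials for shares of 20% to 40%.

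**Step 2: effect on the estimate.** Shift = imbalance × setting effect.
- Typical (one SD) with a 5-point setting effect: 0.066 × 5 = 0.33 at 20%, 0.075 × 5 = 0.375 at 30%, 0.080 × 5 = 0.40 at 40%.
- Uncommon, 15-point imbalance: 0.15 × 5 = 0.75 points.
- In SD units, a 10-point imbalance with a setting effect of 0.2 to 0.5 SD gives 0.02 to 0.05 SD, against the planned 0.5.

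**Step 3: compare with sampling error.** The 10-week interval of the earlier trial implies a standard error of (7.5 − 2.0)/(2 × 1.96) = 1.40 with 300 patients. Scaled to 150 patients this is 1.40 × √2 = 1.98. The share of variance due to setting imbalance is then 0.33²/1.98² = 2.8% to 0.40²/1.98² = 4.1%.

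**Step 4: what accounting for setting gains.** With a setting effect of g within-setting SDs, setting explains R² = p(1 − p)g²/(1 + p(1 − p)g²). At p = 0.3 and g = 0.5 this is 0.0525/1.0525 = 0.050. The effective standardised effect rises from 0.5 to 0.5/√0.950 = 0.513. Power at 75 per arm, with an assumed two-sided 5% test and no dropout, rises from 0.860 to 0.877. For shares of 20% to 50%, adjusted power is about 0.863 to 0.864 at g = 0.2 and 0.873 to 0.880 at g = 0.5.

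**Step 5: after stratifying.** With blocks of 4, an incomplete block can leave the arms at most 2 patients apart in a stratum. The difference in community share is then held to about 2/75 = 2.7 points.

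**The case against.** The strongest reply is that the protocol contains no error here. Chance imbalance in an unstratified factor occurs in every randomised trial. It is not bias, and the standard error and type I error rate already cover it. That stands in full.

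Three further points also stand. The planned baseline adjustment already removes any part of a setting difference that shows in baseline Oswestry, so the 5 points must be what remains afterwards. A setting covariate alone, which a statistical analysis plan could add, would recover most of the precision. And no planned analysis asks whether the effect holds in each setting, so the case cannot rest on that.

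A reader might also infer that one unstratified list is used. Section 2.9 does not say so: it is silent on strata and on the number of lists. Nor do the documents show that the two sources differ in prognosis. The background concerns seeking care and choosing therapy, not outcome, and both streams meet the same eligibility criteria.

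What the reply does not remove is timing. A covariate can be added later, but the allocation list cannot be changed once patients have been randomised.

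**Conclusion.** This holds as a minor, cheap improvement. Two settings are used, no stratification by setting is named, and the model as described has no setting term. The arms can then differ in community share with an SD of about 6.5 to 8 percentage points at assumed shares of 20% to 40%. The cost is a little precision: typically under 0.5 Oswestry points, or about 3% to 4% of the variance, if setting shifts the outcome by an assumed 5 points after baseline adjustment. The effect scales with that assumption and disappears if setting is not prognostic.

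Two stronger conclusions are tempting and should not be drawn. The treatment estimate is not biased and the trial's validity is not in question. The 0.75-point shift, 14% to 17% of the earlier trial's effects (0.75/5.4 to 0.75/4.3), is not an expected distortion: it needs both a 15-point imbalance, seen in about 2% to 6% of trials, and the full assumed setting effect.

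**What to change.** In section 2.9, state that block randomisation is stratified by setting (hospital OPD versus community centre), with a separate concealed list and set of envelopes for each stratum, generated in the web-based software already planned. Under Analysis of patients' clinical outcomes, add setting as a covariate in the linear mixed model, so that the analysis matches the allocation and takes the gain in precision.

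The cost is one sentence in each section, two lists to administer instead of one, and possibly one incomplete block per stratum. The sample size does not change. The list has to be set up before the first randomisation. If randomisation has already begun, adding the covariate alone recovers most of the benefit.
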